### Sample size

The sample size calculation is based on the primary outcome of OSFD within the first 14 days. Assuming the HDIVC group would gain 2 additional OSFD days compared to the control group (SD 5 days), with a two-sided *α* of 0.05 and power of 0.80, the initial calculation using the formula for two independent sample means required 98 patients per group. To account for non-normal distribution of OSFD, the Pitman asymptotic relative efficiency correction expanded the sample by 15% to 113 per group. Allowing for a 5% dropout rate, the final sample is 238 patients (119 per group). The study plans to recruit 10 patients per month over 24 months. Ethical approval has been gained in participating centers. Centralized online training has been completed to ensure protocol adherence. As of May 30, 2026, the lead center has recruited 34 patients. Participating centers are being activated, which will increase recruitment capacity.

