### Randomization and blinding

Participants will be strictly enrolled based on predefined eligibility criteria. Stratified block randomization will be employed by each research center. Patients will be allocated to either the HDIVC group or control group, with allocation concealment maintained throughout. Randomization numbers will be generated by statisticians using SAS 9.4 software, employing block randomization within each stratum to ensure balanced group assignment. Expansion of the sample size may be considered if necessary.

Stratification is performed at three levels: (1) participating center (8 centers), and (2) etiology, categorized as biliary, hypertriglyceridemic, alcoholic or other. Due to our rigorous inclusion criteria, all enrolled patients are diagnosed with SAP. We will not proceed stratification by disease severity. The randomization sequence is generated independently for each stratum combination (8 × 4 = 32 strata) by an independent statistician using SAS 9.4, employing variable block sizes of 4 and 6 (randomly alternated) to ensure allocation concealment and balance within each stratum.

To ensure blinding, study medications—either 50 mL vitamin C solution or matching placebo (0.9% normal saline)—will be prepared in identical, opaque, light-proof containers by UDPN according to the randomization list. Both groups will receive equal volumes (50 mL) via identical administration protocols using the standardized micropump (2 g/h). Crucially, the administration through a central vein minimizes potential sensory cues (such as infusion site irritation) that could arise from pH differences, thereby maintaining the blind for participants, clinical staff, and data analysts. All centers will follow this standardized protocol after thorough training and the study medicine is provided by one center to avoid bias.

The data management and analysis will implement a two-stage unblinding process. After all data have been locked following blinded data verification, the group assignments for each participant will be disclosed for statistical analysis. When the statistical analysis completes, the specific group assignments (intervention group or control group) will be disclosed to assess the study outcomes.

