### Data collection and management

To accurately capture the true severity and clinical heterogeneity of severe acute pancreatitis, comprehensive baseline and dynamic clinical parameters will be systematically recorded in the electronic Case Report Forms (eCRF). These explicitly include: (1) pancreatic enzyme levels over time; (2) daily APACHE II and SOFA scores; (3) the exact degree of extrapancreatic organ involvement and specific organ failures (e.g., respiratory, cardiovascular, and renal impairment); and (4) the requirement and duration of advanced therapeutic interventions, specifically including mechanical respiratory support, hemodynamic support (vasopressors), and CRRT. Recording these decisive clinical variables ensures a rigorous evaluation of the true therapeutic value of HDIVC in the overall care of SAP. Missing data for the primary and secondary outcomes will be addressed using multiple imputation by chained equations (MICE), assuming the data are missing at random. If not, last observation carried forward (LOCF) will be used. Source documents will be maintained for verification. The database will be locked after monitoring and queries resolution for final analysis.

Fecal samples will be collected within 24 h of enrollment (baseline), on treatment Day 7, and on Day 14. Samples will be frozen at −80 °C and shipped to the central laboratory. Total genomic DNA will be extracted, and the V3–V4 hypervariable region of the 16S rRNA gene will be PCR-amplified and sequenced by a certified sequencing service provider.

To minimize inter-center variability, concomitant treatments such as fluid resuscitation and antibiotic use will be guided by the same recommendations for severe acute pancreatitis management (21). Although minor variations reflecting local practice are expected, adherence to a standardized framework will be reinforced through investigator training and regular monitoring. All concomitant therapies will be prospectively recorded, and potential confounding effects will be addressed through statistical adjustment in the final analysis. Center will be included as a random intercept in the primary mixed-effects model to account for clustering of patients within centers.

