### Statistical methods

The statistical analysis will follow an intention-to-treat (ITT), per-protocol (PP), and safety population approach. All statistical tests will be two-sided, with a *p*-value < 0.05 considered statistically significant. Baseline characteristics will be summarized using descriptive statistics. For quantitative variables, descriptive statistics will include calculations of mean, standard deviation, median, minimum, maximum, and interquartile range (IQR). For categorical variables, descriptive statistics will report frequencies and percentages for each category.

The primary outcome, OSFD within the first 14 days, will be analyzed using a linear mixed-effects model with center included as a random intercept, allowing quantification and adjustment for between-center variability. Sensitivity analyses will treat center as a fixed effect or omit center effects to assess robustness. A treatment-by-center interaction test will be performed to evaluate heterogeneity of treatment effect across sites. The intraclass correlation coefficient (ICC) from the null model will be reported. To control the familywise type I error rate for secondary outcomes, a hierarchical (fixed-sequence) testing procedure is applied. The pre-specified order is: (1) ICU all-cause mortality, (2) SOFA score at Day 7, (3) C-reactive protein at Day 7, (4) APACHE II score at Day 7, followed by all remaining secondary outcomes. Each outcome is formally tested only if all preceding outcomes in the hierarchy reach statistical significance at the two-sided *α* = 0.05 level. Outcomes below the hierarchical chain—including cytokine levels (IL-6, IL-1, IL-10), BISAP score, CTSI score, ICU length of stay, hospitalization costs, and gut microbiota composition—are designated as exploratory. Their *p*-values will be reported descriptively without formal inferential claims.

Bioinformatics processing will use QIIME2 with DADA2 denoising to generate amplicon sequence variants (ASVs), and taxonomic assignment will be performed against the SILVA database. Alpha diversity (Shannon, Chao1 indices) will be compared between groups using Wilcoxon rank-sum tests. Beta diversity (Bray-Curtis, UniFrac distances) will be visualized by principal coordinate analysis (PCoA) and tested by PERMANOVA. Differential abundance analysis will be conducted using LEfSe (LDA > 2.0) and MaAsLin2. Longitudinal changes will be analyzed using linear mixed-effects models if serial samples are available.

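### The unadjusted Wilcoxon test for alpha diversity leaves the baseline stool sample and the randomisation strata unused, which gives away power on an exploratory outcome

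*Protocol article*

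**What the plan says.** All places are in the protocol article.

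- **Alpha diversity (Statistical methods):** "Alpha diversity (Shannon, Chao1 indices) will be compared between groups using Wilcoxon rank-sum tests".
- **Beta diversity (same paragraph):** Bray-Curtis and UniFrac distances are to be "visualized by principal coordinate analysis (PCoA) and tested by PERMANOVA". No model terms and no permutation scheme are given.
- **Other microbiota methods (same paragraph):** LEfSe and MaAsLin2 for differential abundance, and linear mixed-effects models for change over time, the latter only if serial samples are available. The terms of these models are not given.
- **Sampling (Data collection and management):** "Fecal samples will be collected within 24 h of enrollment (baseline), on treatment Day 7, and on Day 14".
- **Randomisation (Randomization and blinding):** "The randomization sequence is generated independently for each stratum combination", that is 8 centres by 4 etiologies, 32 strata, with blocks of 4 and 6.
- **Level (Statistical methods):** "All statistical tests will be two-sided, with a *p*-value < 0.05 considered statistically significant".
- **Status:** gut microbiota composition is the tenth secondary outcome. Statistical methods then names it among the exploratory outcomes, whose p-values are descriptive only.

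**The concern.** The design creates two sources of precision for this outcome: a baseline value for each patient, and balance of the arms within centre and etiology. The test that the article fixes for alpha diversity can use neither. The primary outcome, by contrast, gets a random intercept for centre.

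An outcome usually correlates with its own baseline, and a comparison of follow-up values alone leaves that explained variation in the noise. If diversity also differs by hospital or etiology, the stratified allocation removes that variation from the true sampling error of the group difference, but an unadjusted test still counts it. At stake is a missed signal in an outcome for which the samples and sequencing are planned anyway. No confirmatory claim is at stake.

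**Working it through.** **The plan's own figures.** No effect, power or sample size is stated for the microbiota, so the only figure to reproduce is the primary sample size. Its effect input reads "Assuming the HDIVC group would gain 2 additional OSFD days compared to the control group (SD 5 days". The error rates are a 5% level, tested on both sides, and 80% power.

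- n per group = 2 × [5 × (1.960 + 0.842) / 2]² = 98.1. The article says "required 98 patients per group"; rounding up gives 99, an immaterial difference.
- 98 × 1.15 = 112.7, so 113; 113 / 0.95 = 118.9, so 119 per group and 238 in total.

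The chain reproduces, and N = 238 is carried forward.

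**Assumed inputs (not in the article).**

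- Share *s* of diversity variance explained by centre plus etiology: 0, 7, 15 or 30%.
- Within-stratum correlation *r* of baseline with follow-up: 0.5 for power; 0 and 0.5 for the level, plus 0.7 in one check.
- True shift: 0.37 of the total SD. This is about what a Wilcoxon test detects with 80% power at N = 238: 2.802 × √(4/238) = 0.363, divided by √0.955 for its efficiency under normality = 0.372.
- Every patient gives both samples; normal outcome; 8 equal centres; etiology mix 40/35/10/15%; blocks of 4 or 6 within 32 strata.

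**Level when the strata are ignored.** The variance of the group difference shrinks by a factor of about 1 − *s*, but the test does not know this. Its level is about 2 × [1 − Φ(1.96 / √(1 − *s*))]. The simulation used 4,000 null trials per scenario; the range is over *r* = 0 and 0.5.

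| Strata share | Formula | Wilcoxon, simulated |
|---|---|---|
| 0% | 5.0% | 4.5–5.1% |
| 7% | 4.2% | 4.2–4.4% |
| 15% | 3.4% | 3.5–3.6% |
| 30% | 1.9% | 1.5–2.4% |

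Models that include the strata, with or without baseline, stay at 4.6–5.4% throughout.

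**Level when only baseline is ignored.** With no strata effect and *r* = 0.7, the Wilcoxon level is 5.03% (12,000 trials). Omitting baseline does not lower the level.

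**Power.** With strata and baseline in the model, the residual variance is (1 − *s*)(1 − *r*²) and power is about Φ(0.37 / √(4 × residual variance / 238) − 1.96).

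- At *s* = 0: residual variance 0.75, SE 0.1123, ratio 3.30, power 91%.
- At *s* = 30%: residual variance 0.525, SE 0.0939, ratio 3.94, power 98%.

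Simulated power (1,000 trials per row, *r* = 0.5):

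| Strata share | Wilcoxon | Strata only | Strata + baseline |
|---|---|---|---|
| 0% | 78% | 79% | 90% |
| 7% | 79% | 83% | 93% |
| 15% | 79% | 85% | 94% |
| 30% | 81% | 93% | 98% |

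The two omissions separate cleanly. Adding the strata gains about 0, 4, 6 and 12 points. Adding baseline on top gains about 11, 10, 9 and 5 points.

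**PERMANOVA.** This was approximated by Euclidean distance on 8 features, with 600 null trials and 199 permutations each (simulation error about 0.9 points). At shares of 0, 7, 15 and 30%, free permutation rejects in 6.0, 4.0, 2.7 and 1.7% of trials. Permutation within strata rejects in 4.7–6.3%. These figures show what free permutation would do; the article does not say that it will be used.

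**The case against.** The strongest reply is that nothing the trial claims depends on this. The article names gut microbiota as exploratory, with p-values for description only. A conservative test breaks no error-rate promise there, and neither the primary outcome nor the four named steps of the testing hierarchy is touched. That stands, and it sets the severity.

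It is also fair that the Wilcoxon test is not the only analysis. Baseline, Day 7 and Day 14 samples are scheduled, so the longitudinal mixed model is the expected case and would draw on the serial samples, and MaAsLin2 accepts covariates. But the terms of these models are not given, the mixed model is conditional, and it is stated for change over time. Neither replaces the named between-group test of alpha diversity.

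Three stronger readings are tempting, and the article does not support them:

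- **That both omissions push the tests below 5%.** Only the strata can do so, and only if centre or etiology is related to diversity. The article gives no figure for that. With no such relation the simulated levels show no shortfall.
- **That the planned PERMANOVA ignores the strata.** The method accepts covariates and restricted permutation. The article neither states nor excludes them, and such detail may lie in an analysis plan that is not shown.
- **That a null microbiota result would be an artefact of the test.** At the assumed shift the Wilcoxon test still has about 78–81% power. It is less sensitive than it could be, not uninformative.

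**Conclusion.** The point holds as a minor efficiency matter. For alpha diversity the article fixes a test that cannot use the baseline sample or the randomisation strata. Under the stated assumptions this gives up about 12 points of power when the strata explain nothing (78% against 90%) and about 16–17 points when they explain 30% (81% against 98%).

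The gain from baseline depends on the assumed correlation of 0.5 and vanishes as that correlation goes to zero. The gain from the strata depends on the assumed variance share. The absolute powers also assume that all 238 patients provide samples; fewer samples would lower every column. Any error in the level is conservative and falls on descriptive p-values. For PERMANOVA the conclusion is only that the terms and permutation scheme should be stated.

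**What to change.** **Alpha diversity.** Make the main comparison a linear model for Shannon and for Chao1 (transformed if skewed), at Day 7 and separately at Day 14, with treatment, the baseline value of the same index, centre and etiology. Keep the Wilcoxon test as a sensitivity analysis. A stratified rank test (van Elteren) would deal with the strata but not with baseline.

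**Beta diversity.** Run PERMANOVA separately at each visit, so that repeat samples from one patient are never treated as independent. Enter centre and etiology before treatment, and restrict permutations to within randomisation strata, or within centre where strata are too sparse.

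**Cost.** No extra samples, visits or patients. The plan needs a simple rule for patients without a baseline sample and a few lines of code. The model spends 13 coefficients (intercept, treatment, baseline, 7 for centre, 3 for etiology), which is little against 238 patients. The database is not yet locked, so the change can be written down before unblinding.

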### Interim analysis and data monitoring committee

An interim analysis will be conducted when approximately 50% of participants have completed the primary outcome assessment. The analysis will use O’Brien–Fleming boundaries, with nominal alpha spending to control the overall type I error rate. Predefined statistical thresholds for efficacy and futility will be used to guide recommendations. An independent Data Monitoring Committee (DMC), including experts in pancreatitis, clinical trials, and statistics, will oversee patient safety, trial conduct, and data integrity. The DMC will operate under a formal charter that specifies its responsibilities, decision-making procedures, meeting frequency, reporting of adverse events (Supplementary material 1). The committee will have the authority to recommend continuation, modification, or early termination of the trial based on interim findings. All interim analyses will be conducted by statisticians independent of the study team, and results will remain blinded to investigators until the trial is completed.

### Safety and adverse event reporting

Safety will be assessed by collecting and recording adverse events (AEs), changes in vital signs, laboratory parameters (including blood, urine, and biochemical tests), and systemic reactions during the treatment period.

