## Method and analysis

### Study design

This prospective, randomized, double-blind, multicenter trial will investigate whether early intravenous HDIVC reduces OSFD within the first 14 days in SAP patients. We will enroll 238 participants (119 per group) from eight hospitals across China, with block randomization allocating patients to either HDIVC or control groups. Serial assessments of organ function, disease severity scores, and mortality will be evaluated at predefined time points before and after treatment to determine therapeutic efficacy. The evaluation and examination will be continued from randomization to 180 days or death. Figure 1 shows the flow chart of the study. This study protocol is written according to the Standard Protocol Items for Randomization Trials (SPIRIT) statement (18).

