### Intervention

Human pharmacokinetic data indicate a linear relationship between dose and plasma peak concentration. Continuous infusion at higher daily doses is required to sustain plasma levels considered necessary for antioxidant and endothelial effects (19). Our preliminary data revealed a critical dose–response discrepancy: while a dosage of 200 mg/kg effectively improved inflammatory biomarkers in patients with MSAP, no comparable clinical benefit was observed in the SAP cohort (6). This divergence suggests that SAP represents a catastrophic ‘Redox Storm’, where the production of ROS exponentially overwhelms the neutralizing capacity of conventional regimens. Vitamin C exhibits a linear dose-concentration relationship in critically ill patients. Continuous infusion provides stable steady-state plasma concentrations proportional to the daily dose (20). Notably, a comprehensive scoping review has validated the safety of ultra-high-dose intravenous vitamin C, reporting an average well-tolerated dosage of 455 mg/kg/d (ranging from 260 to 925 mg/kg/d) across critically ill and oncological populations (21). Guided by this safety benchmark of 455 mg/kg/d, we have escalated our study dose to 500 mg/kg per 24 h (administered from 06:00 to 06:00 the following day) for 7 consecutive days, aiming to surpass the therapeutic threshold and capture a definitive treatment effect in SAP.

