#### AEs include

(1) presence of urinary crystals.(2) occurrence of acute kidney injury (AKI) as defined by KDIGO criteria.(3) clinical or laboratory signs of unexpected hemolytic anemia (e.g., sudden hemoglobin drop combined with elevated indirect bilirubin), specifically to monitor for undetected G6PD deficiency.

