#### Treatment discontinuation criteria

Study drug infusion must be discontinued immediately for any of the following events. Emergency unblinding may be performed if deemed necessary by the attending physician:

(1) new-onset AKI meeting KDIGO Stage 2 or 3 (serum creatinine ≥ 2.0 × baseline or urine output < 0.5 mL/kg/h for ≥ 12 h) judged as potentially related to vitamin C-associated oxalate nephropathy.(2) microscopic urinalysis showing abundant calcium oxalate crystals (≥50 per high-power field) with acute creatinine rise.(3) clinical or laboratory evidence of hemolytic anemia (sudden hemoglobin drop, elevated indirect bilirubin, hemoglobinuria).(4) confirmed hypoglycemia (<3.9 mmol/L) after excluding glucometer interference by venous blood gas confirmation.(5) any SAE judged as possibly or definitely related to the study drug.

Both AEs and SAEs will be evaluated at 8:00 a.m. every day. Investigators are required to promptly assess the aforementioned adverse events. If the investigator determines that an abnormal laboratory result is clinically significant and not part of the clinical condition, it should be recorded as an adverse event and report to the PI of each research site. Once confirmed, the intervention should be discontinued immediately and proper medication should be taken.

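### The only stated adverse event window is the 7-day treatment period, and recording depends partly on attribution, so later or disease-ascribed kidney injury has no stated route into the safety comparison between arms.

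*Protocol article*

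**What the plan says.** Four parts of the protocol article set the rules for recording harm.

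- **Window.** Safety and adverse event reporting lists adverse events, vital signs, "laboratory parameters (including blood, urine, and biochemical tests), and systemic reactions during the treatment period". The Intervention section fixes the length of treatment: "administered from 06:00 to 06:00 the following day) for 7 consecutive days". No other window for adverse events or SAEs is given. Under Study design, evaluation is "continued from randomization to 180 days or death".
- **Named events.** The list of AEs includes "occurrence of acute kidney injury (AKI) as defined by KDIGO criteria" and "presence of urinary crystals". Neither carries a causality condition.
- **Laboratory rule.** The closing paragraph of Treatment discontinuation criteria says that if the investigator finds that an "abnormal laboratory result is clinically significant and not part of the clinical condition, it should be recorded as an adverse event". It also calls for a daily review of AEs and SAEs and gives no end day for it.
- **Safety outcome.** Item 9 of Secondary outcome covers adverse events attributed to vitamin C, not all adverse events.

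Table 1 schedules laboratory biomarkers (including renal function), continuous renal replacement therapy (CRRT) and SOFA on Days 0, 1, 3, 7, 14 and 28, and death at Day 180. Under Primary outcome, renal replacement therapy (RRT) over 14 days counts against organ support-free days.

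**The concern.** Every patient enters with persistent organ failure, so a rise in creatinine during the study can readily be put down to pancreatitis. A randomised, blinded comparison does not need a causality judgement for each patient: an excess in one arm shows in the totals. If attribution decides whether an event is recorded or reported, the events most easily lost are drug-caused ones that look like the disease.

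The window adds to this. Renal harm that appears or is recognised after the last infusion day falls outside the only collection period stated, although patients are followed well beyond it.

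The events affected are ones the article itself watches for. Oxalate deposition, oxalate nephropathy and AKI appear in the Intervention, Randomization and blinding, AE list and Treatment discontinuation sections. The Discussion cites a sepsis trial in which a lower dose raised the risk of death or persistent organ dysfunction (RR 1.21, 95% CI 1.04–1.40). An incomplete adverse event comparison could therefore make the intervention look safer than it is.

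**Working it through.** **1. Length of the stated window against the other horizons.** The inputs are 7 treatment days (Intervention), 14 primary-outcome days (Primary outcome), Day 28 as the last scheduled laboratory visit (Table 1) and 180 days of follow-up (Study design).

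- 7/14 = 50% of the primary-outcome period
- 7/28 = 25% of the time to the last laboratory visit
- 7/180 = 3.9% of follow-up

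These are shares of calendar time, not of risk.

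**2. The rules applied to typical cases.**

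| Event | Rule that captures it | Rule that may drop it |
|---|---|---|
| KDIGO AKI on Day 4, ascribed to pancreatitis | AE list, without condition | Laboratory rule (part of the disease); safety outcome (not attributed to the drug) |
| KDIGO AKI first arising on Day 10 | AE list, if it applies after treatment | Stated window |
| Non-fatal SAE on Day 20 | Daily review, if it continues | Stated window |
| Death on Day 60 | Table 1, Day 180 | None |

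In the first row, the AE list and the laboratory rule can give opposite answers for the same creatinine-defined event. Even if the AE list prevails and the event is recorded, the wording of the safety outcome can still leave it out of the comparison.

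**3. What other data already capture.** Renal function, CRRT and SOFA at Days 14 and 28 are collected in all patients whatever the attribution. RRT to Day 14 is in the primary outcome, but merged with vasoactive drugs, ventilation and death, and it shows only kidney injury that led to RRT. The article does not say that the Day 14 and Day 28 renal data will be compared between arms as safety results.

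**4. Sensitivity to incomplete capture (assumed rates).** No stated figure depends on this point. The group size used here reproduces: 2 × (5 × (1.960 + 0.842)/2)² = 98.1; 98.1 × 1.15 = 112.8, so 113; 113/0.95 = 118.9, so 119. The article gives no AKI rate and no timing of events, so the rates and capture shares below are assumptions, with the same share f captured in both arms. Power = Φ{[Δ − 1.96√(2p̄(1−p̄)/n)] / √[(p₀(1−p₀) + p₁(1−p₁))/n]}, with n = 119, both rates multiplied by f, Δ their difference and p̄ their mean.

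| Assumed AKI rates | f = 1 | f = 0.75 | f = 0.50 | f = 0.25 |
|---|---|---|---|---|
| 10% vs 20% | 0.580 | 0.448 | 0.309 | 0.172 |
| 15% vs 30% | 0.795 | 0.641 | 0.448 | 0.240 |

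The table shows the direction and steepness of the effect. It does not estimate what this trial will lose.

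**The case against.** The strongest reply has four parts.

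- **The AE list is unconditional.** It names KDIGO AKI and urinary crystals as adverse events outright. The laboratory rule can be read as a residual test for other abnormal values, in which case the two do not conflict. This is a fair reading, and it rules out saying that laboratory events count only if judged separate from the disease. But the text does not say which rule governs a creatinine-defined AKI, eight centres may differ, and the safety outcome filters by attribution on either reading.
- **Later kidney data exist.** Renal function, CRRT and SOFA run to Day 28, RRT to Day 14 is in the primary outcome, and death is recorded at Day 180. A reader might infer that kidney harm after Day 7 is lost altogether. The document does not support that: the data will be in the database.
- **The window is not explicit.** The phrase about the treatment period could attach only to the last item in its sentence, and the daily review has no end day. The 7-day window is the natural reading, not a stated exclusion of later events. A rule open to both readings still needs fixing.
- **This is a condensed article.** The full protocol or the data monitoring committee charter may set a longer window. So one cannot conclude that the committee's view of harm is restricted. The attribution limit on the safety outcome and the unclear relation between the two recording rules are, however, in the published text.

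**Conclusion.** The point stands in limited form and is worth correcting. As written, the only stated collection window is 7 days, the safety outcome is restricted by attribution, and the laboratory rule is in tension with the AE list. AKI or non-fatal SAEs that first arise after Day 7, or that are ascribed to pancreatitis, therefore have no stated route into the safety comparison between arms.

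The window covers 25% of the time to the last scheduled laboratory visit. The share of events lost cannot be estimated, because the article gives no event rates or timing. It does not support any specific number of missed AKI events.

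The conclusion assumes that the treatment-period phrase governs the whole safety sentence and that no unseen document sets a longer window. If the second assumption fails, the window part falls away, but the attribution part remains.

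**What to change.** 1. State that AEs and SAEs are collected from randomisation to at least Day 28, the last scheduled laboratory visit. Death is already recorded at Day 180.
2. Derive KDIGO stage at baseline and at each scheduled laboratory visit for every patient regardless of attribution. Report new or worsened AKI and new RRT by arm. The baseline stage matters because some patients will enter with renal failure.
3. Compare all AEs between arms. Record causality in a separate field, not as a condition for recording or reporting.
4. Reconcile item 9 of Secondary outcome, the AE list and the laboratory rule under Treatment discontinuation criteria. That last paragraph also ties confirmation of an event to stopping the infusion, so the recording rule should be worded separately. This point proposes no change to any stopping rule.

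The cost is protocol wording and a longer AE form. Renal function and CRRT to Day 28 are already scheduled, so no new procedure is needed and the sample size stays at 238. The downside is more AE records, most of them disease-related.
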